**Methods:**

This is a monocentric pilot study taking place in Bangor, Wales, United Kingdom. We plan to enroll up to 100 adult survivors of cancer not receiving toxic anticancer treatment, who will provide self-reported behavioral data recorded via a dedicated app and validated questionnaires and objective data automatically collected by a paired smartwatch over 16 weeks. The participants will continue with their normal routine surveillance care for their cancer. The primary end point is feasibility (eg, mHealth monitoring acceptability). Composite secondary end points include clinically relevant patient-reported outcome measures (eg, the Edmonton Symptom Assessment System score) and objective physiological measures (eg, step counts). This trial received a favorable ethical review in May 2023 (Integrated Research Application System 301068).

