### Primary Outcome

The main outcome of this trial is to assess the feasibility of mHealth monitoring in survivors of cancer not receiving toxic anticancer treatment. A priori criteria based on a traffic light system will be used to determine whether mHealth monitoring is unfeasible and future trials should be halted (red), whether changes to the study design or mHealth intervention are required before future trials are initiated (amber), or whether mHealth monitoring is considered feasible, and progress to future trials can occur without modification of the study design or intervention (green) [35]. The traffic light system will be applied at the end of the 16-week study period following collection of the last follow-up assessment from the last participant (on an intention-to-treat basis) to the following feasibility outcomes: eligibility (no set criteria but number of patients screened and eligible will be recorded); recruitment rate (green: n =>75, amber: n =≥50, and red: n=<50); acceptability of randomization and assessment procedure (no set criteria but the characteristics [and the proportion by group] of participants withdrawing post randomization will be captured); mHealth acceptability (green: ≥50/100, ≥50% of participants engage with the app at least once a week on at least 12 weeks out of the 16-week study, amber: ≥50/100, ≥50% of participants engage with the app at least once a week on at least 8 weeks out of the 16-week study, and red: <50/100, <50% of participants engage with the GK app at least once a week on at least 8 weeks out of the 16-week study); attrition rate (green: 20/100, <20% dropout rate, amber: ≤40/100, ≤40% dropout rate, and red: <40/100, >40% dropout rate); and missing data (green: <20/100, <20% of data missing, amber: ≤40/100, ≤40% of data missing, and red: >40/100, >40% of data missing). Engagement with the GK app is defined as logging on and completing at least 1 of the scheduled measures (ESAS, food intake, or habitual physical activity).

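### The red attrition threshold contradicts itself (below 40/100 and above 40%), and the green threshold does not match its own percentage

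*Protocol article*

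**What the plan says.** The Primary Outcome section sets out a traffic light, fixed in advance and applied once the last participant has completed follow-up. One of its purposes is to "determine whether mHealth monitoring is unfeasible and future trials should be halted (red"; amber means change before going on, and green means go on unchanged. Attrition is one of the listed feasibility outcomes: "attrition rate (green: 20/100, <20% dropout rate, amber: ≤40/100, ≤40% dropout rate, and red: <40/100, >40% dropout rate".

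The next item in the same sentence uses the same cut-offs for another quantity: "missing data (green: <20/100, <20% of data missing, amber: ≤40/100, ≤40% of data missing, and red: >40/100, >40% of data missing". The attrition thresholds appear nowhere else in the article, so no other section settles which half of each band governs.

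**The concern.** A progression rule fixed in advance is useful only if it gives one answer for each result. Here the two halves of red point in opposite directions, and the two halves of green do not share a boundary. Someone applying the fractions and someone applying the percentages would report different colours for the same dropout count. Ten dropouts among 100, for example, is green by percentage but meets the printed red fraction.

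The colours feed the decision on whether later trials stop, change or proceed. If the wording is repaired only after dropout is known, the repair can look as if it was chosen to suit the result.

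**Working it through.** **Inputs.** The thresholds come from the Primary Outcome section, and the intended sample size of 100 from Statistical Considerations. No figure that the article calculates bears on this point. Its confidence interval half-width for engagement does reproduce (1.96 × √(0.5 × 0.5/100) = 0.098, stated as 10%), but it plays no part here.

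**Step 1: compare the halves of each band.** Let x be the number of dropouts among n = 100, so that x/100 equals x%.

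- Red requires x < 40 and x > 40. No x satisfies both.
- Green requires x = 20 (the fraction as printed, with no sign) and x < 20. No x satisfies both.
- Amber requires x ≤ 40 in both halves. These agree.

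**Step 2: classify every count from 0 to 100.**

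| Dropouts (n = 100) | Fractions as printed | Percentages, read in order |
|---|---|---|
| 0–19 | amber and red | green |
| 20 | green, amber and red | amber |
| 21–39 | amber and red | amber |
| 40 | amber | amber |
| 41–100 | no band | red |

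Forty is the only count that the fractions place in exactly one band.

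- Reading the fractions in order does not rescue them. Green takes 20, amber takes every other count up to 40, red is never reached, and 41 to 100 still have no band.
- If either half is enough, 0 to 20 can be green, amber or red, 21 to 39 amber or red, 40 is amber, and 41 to 100 are red.
- If both halves are required, 0 to 40 are amber, 41 to 100 have no band, and neither green nor red can occur.

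The missing sign before the green fraction may have been lost when the text was read from PDF. If it was a less-than sign, green is consistent and only red is wrong. The red contradiction does not depend on this, because both red signs are present and they conflict.

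**Step 3: compare with the missing-data rule.** Its fractions are <20/100, ≤40/100 and >40/100, beside <20%, ≤40% and >40%. Read in order at n = 100, both forms give 0–19 green, 20–40 amber and 41–100 red. This is the same classification as the attrition percentages.

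**Step 4: check whether a sample below 100 creates a further conflict.** Enrolment is described as "We plan to enroll up to 100 adult survivors of cancer", and recruitment is graded as "recruitment rate (green: n =>75, amber: n =≥50, and red: n=<50", so n may be below 100. Take n = 76:

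- 35 dropouts: 35/76 = 0.461, above 40/100 and above 40%. The fraction and the percentage agree.
- 45 engaged: 45/76 = 0.592, above 50/100 and above 50%. They agree again.

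Read as a proportion, the fraction gives no second answer at a smaller n.

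**The case against.** The best defence is that this is an evident slip of sign. The percentage beside the red fraction, the amber band before it and the missing-data rule after it all point the same way, and nobody could credibly report 10% dropout as red. Attrition is also only one of several descriptive criteria. Statistical Considerations treats engagement as the most important and bases the sample-size precision on it. No test, estimate or sample size depends on the attrition band. Contingency Plans adds that no other study within the GATEKEEPER project is waiting on this one, although Strengths and Limitations does foresee a randomised study if feasibility is shown.

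Most of this stands, and it limits the weight of the point. It does not make the printed criterion correct. A reader should not have to infer a progression threshold from a neighbouring rule.

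Three stronger readings are tempting, and the article does not support them:

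- **The whole attrition traffic light is inverted.** Only the red fraction runs the wrong way. The percentages, read in order, classify every dropout rate. The green and amber overlap arises because amber has no printed lower bound. The recruitment and missing-data rules share that convention, and ordered reading resolves it. A count that can take any of the three colours is limited to 0 to 20 dropouts.
- **A trial with excellent retention would be told to halt.** That requires using the red fraction and ignoring the percentage printed beside it.
- **Every figure over 100 breaks down when fewer than 100 enrol.** The article uses x/100 to restate a percentage. It does so for the engagement target in the abstract, Objectives and Statistical Considerations, and for shares of data, where 100 cannot be a number of people. A conflict appears only if the denominator is discarded and the numerator treated as an absolute count.

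**Conclusion.** The point holds as an internal contradiction in one criterion. Red attrition cannot be met as printed, and green as printed does not match its own percentage. At n = 100, the printed fractions place 40 counts (0 to 39) in red that the percentages call green or amber, and leave 60 counts (41 to 100) in no band.

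The likely intent is clear from the percentages and the missing-data rule, so this is a correction of wording. It does not show that the design or the cut-offs are unsound. It matters because the criterion is a stop, modify or go threshold fixed in advance within the primary outcome. I do not assume that red on attrition alone would decide the overall result.

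The acceptability and missing-data rules are internally consistent and need no correction. The conclusion rests on reading x/100 as a proportion, as the article does elsewhere, and on the article being the only text available. If the full protocol already has the right signs, only the article needs correcting.

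**What to change.** Before the traffic light is applied, restate the attrition criterion so that both forms agree and the bands do not overlap:

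- green: below 20% (<20/100)
- amber: 20% to 40% inclusive
- red: above 40% (>40/100)

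Give each as a percentage of all enrolled participants, which fits the intention-to-treat basis that the section already states. This keeps the article's own percentage cut-offs.

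Optionally, add that figures over 100 are proportions of those enrolled. That is a clarification and corrects no error.

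The cost is one sentence, with no new data, no change to the sample size and no effect on participants. Dating the correction before dropout results are known protects it from looking outcome-driven.

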**Objective:**

This observational pilot study aims to assess the feasibility of mHealth multidimensional longitudinal monitoring in survivors of cancer. The primary objective is to test the compliance (user engagement) with the monitoring solution. Secondary objectives include recording clinically relevant subjective and objective measures collected through the digital solution.

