**Conclusions:**

In a population with potentially complex clinical needs, this pilot study will test the feasibility of multidimensional remote monitoring of patient-reported outcomes and physiological parameters. Satisfactory compliance with the use of the app and smartwatch, whether confirmed or infirmed through this study, will be propaedeutic to the development of innovative mHealth interventions in survivors of cancer.

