#### Web Portals and Tablets

To complement the data collected by the SH app, Samsung Galaxy watch, and GK app, the patients will fill in questionnaires. These questionnaires will be completed by patients using a tablet, and paper forms will be provided in cases where a tablet is not available. The questionnaires will cover data describing HRQoL, symptoms, sleep, and patient feedback on care. Patients will also use an web-based survey platform (Qualtrics) to fill in questionnaires about habitual physical activity, any structured exercise completed, and patient activation.

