**Figure 1 figure1:**
[figure not shown]
Study schematic of the trial design (longitudinal and observational) with features of the patient-generated data collected through the smartwatch (objective and mostly continuous) and app (subjective and repeated measures or snapshots).

If a patient obtains a higher than predicted maximal heart rate during exercise, the actual maximal heart rate will replace the predicted maximal heart rate. The resting heart rate will then be recorded automatically by the watch. Heart rate zones will then be used to identify habitual physical activity intensity: very light (<30% heart rate reserve [HRR]), light (30%-39% HRR), moderate (40%-59% HRR), vigorous (60%-89% HRR), and near maximal to maximal (≥90% HRR) [34].

Energy expenditure during structured exercise will be estimated from the power output calculated from the mode of exercise, distance completed, and floors climbed. Other measurements such as body fat percentage, oxygen saturation, and blood pressure will be obtained using the standard features available within the smartwatch and smartphone.

The smartwatch will also prompt the participant to complete the ESAS questionnaire on a daily basis and to self-report the amount of habitual physical activity using the 4 abovementioned unvalidated questions on a weekly basis.

The SH app uses the Samsung Galaxy Watch to monitor sleep patterns, track sleep movements, and generate a sleep score. Additionally, the SH app provides daily goals and coaching programs based on sleep data to help improve sleep habits. Sleep analysis uses Samsung proprietary algorithms currently available through the public release of the SH app.

The SH app also allows the self-logging of the type and timing of meals and snacks. It is possible to set a daily target for caloric intake. After inputting details of the food type and quantity from a menu of common meals, the SH app provides a real-time view of the current calorie count for the day and a summary of the nutritional intake to determine if one is within the recommended levels. Moreover, it provides access to an overall dietary report over the span of a week.

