### Statistical Considerations

The study’s primary outcome is feasibility, which, by design, is assessed by multiple outcomes (as described above). Arguably, the most important of these is patient engagement with the mHealth solution, and we have defined the solution as feasible if at least 50% (50/100) of the participants engage with the app at least once a week in 8 of the 16 study weeks. If we recruit 100 eligible participants, we will be able to estimate an engagement rate of 50% (n=50) with a 95% CI of +10% or −10%, whereby the width of the CI (in percentage) was calculated as follows:

1.96×√(p×(1−p)/n) **(1)**

where p is the percentage (50%) and n is the intended sample size (100). For this feasibility study, we considered this CI appropriate for estimating drop-off rates in future studies. Finally, we considered this sample size suitable for the preplanned exploratory subgroup analyses.

The main analysis of the primary outcome (compliance) will be performed on an intention-to-treat basis. Similarly, the secondary outcomes will be evaluated on an intention-to-treat basis. However, for the secondary outcomes, preplanned subgroup and sensitivity analyses will also be conducted. They will include (1) subgroups with at least 75% (75/100) of available patient-generated data (from the app and the smartwatch combined) to exclude unengaged participants and focus on the most committed participants, (2) subgroups defined by the performance status and presence or absence of evidence of neoplastic disease, and (3) subgroups defined by sex and median age. For the primary outcome, no form of inference will be performed on the missing data, as they provide the main outcome of the study. For secondary analyses, neither mean imputation nor the last observation carried forward will be used [50]. However, based on the proportion of missing data, exploratory analyses including low-rank approximation–based imputation [51] could be performed to ensure that the observed effect sizes remain of the same order of magnitude with this approach as well.

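### One completed entry makes a week engaged, so acceptability can be green while missing data is red, and the plan does not say which prevails or how watch data and Samsung Health entries count.

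*Protocol article*

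**What the plan says.** Under Primary Outcome, the protocol article gives traffic lights for recruitment, mHealth acceptability, attrition and missing data. Eligibility and acceptability of procedures are recorded without thresholds.

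- **Acceptability.** Green is "≥50% of participants engage with the app at least once a week on at least 12 weeks out of the 16-week study". Amber lowers 12 weeks to 8, and red is failure to reach the 8-week level. The counting rule is "Engagement with the GK app is defined as logging on and completing at least 1 of the scheduled measures", and the measures named are ESAS, food intake and habitual physical activity.
- **Missing data.** Green is below 20%, amber up to 40%, red above 40%.
- **Meaning of the colours.** Green lets future trials go ahead unmodified; amber calls for changes first; red stops them.

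Statistical Considerations says that feasibility is judged on several outcomes and ranks engagement first among them. It then continues: "we have defined the solution as feasible if at least 50% (50/100) of the participants engage with the app" at least weekly in 8 of the 16 weeks. The abstract's Results and the Objectives section state the hypothesis at the same 8-week level.

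On scope, the abstract's Objective reads "The primary objective is to test the compliance (user engagement) with the monitoring solution", and its Conclusions refer to "Satisfactory compliance with the use of the app and smartwatch".

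On entry channels, Study Procedures places the daily ESAS in the GK app. For food it says "The SH app also allows the self-logging of the type and timing of meals and snacks". Web Portals and Tablets has patients use a web-based survey platform ("Qualtrics) to fill in questionnaires about habitual physical activity").

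**The concern.** The acceptability light measures minimal contact with the app, whereas the study's purpose needs dense data. The plan models daily ESAS trajectories (Study Procedures), derives circadian parameters from the watch (Secondary Outcomes) and hopes to predict adverse events 3 to 5 days ahead (Study Goals and Expected Findings). One entry a week cannot show that such monitoring works.

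A low bar on one item would matter little if the verdict clearly depended on the others. Here two sections point to different verdicts. A result with acceptability amber and missing data red could be reported as feasible under Statistical Considerations, while Primary Outcome would require changes on the first light and a halt on the second.

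Two gaps in the numerator add to this. A participant who never wears the watch can count as fully engaged, so the engagement figure cannot support a conclusion about the watch. And a week with food logged in SH but no GK log-on may or may not count.

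**Working it through.** **1. The plan's own figure.** Statistical Considerations gives a 95% CI of plus or minus 10% for an engagement rate of 50% with n = 100. Check: 1.96 × √(0.5 × 0.5 / 100) = 0.098, or 9.8 percentage points. The figure reproduces and is not in dispute.

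**2. Scheduled entries.** Frequencies are from Table 1 and Study Procedures:

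| Measure | Per week | Over 16 weeks |
|---|---|---|
| ESAS (daily) | 7 | 112 |
| Food diary (thrice weekly) | 3 | 48 |
| Activity report (weekly) | 1 | 16 |
| Total | 11 | 176 |

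**3. Least that one participant must supply**, at one entry in each qualifying week and none otherwise:

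- Green: 12/176 = 6.8%, so 93.2% missing.
- Amber, the level used in Statistical Considerations: 8/176 = 4.5%, so 95.5% missing.

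**4. Sensitivity to the denominator, at 12 weeks:**

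- ESAS only: 12/112 = 10.7%, 89.3% missing.
- ESAS and activity report: 12/128 = 9.4%, 90.6% missing.
- All of step 2 plus weekly weight, Borg rating and health care encounter question (14 a week, 224 in total): 12/224 = 5.4%, 94.6% missing.

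**5. Whole cohort of 100, on 100 × 176 = 17,600 entries:**

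- 50 participants at 12 entries and 50 at none: 600/17,600 = 3.4%, 96.6% missing; acceptability is green.
- The same at 8 weeks: 400/17,600 = 2.3%, 97.7% missing; acceptability is amber.
- 50 participants at 12 entries and 50 with everything complete: (600 + 8,800)/17,600 = 53.4%, 46.6% missing; acceptability is green.

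All three exceed 40%, so the missing-data light would be red if computed on these entries. The third case shows that the lights can disagree even when half the cohort is perfect.

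**6. What the missing-data light asks on the same entries.** Green (under 20% missing) needs more than 0.8 × 176 = 140.8, so 141 entries, about 8.8 a week. Amber (at most 40% missing) needs at least 0.6 × 176 = 105.6, so 106 entries, about 6.6 a week. The engagement item asks for 12 and 8 in total.

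**7. The two sections side by side.** At 8 of 16 weeks, Primary Outcome gives amber and Statistical Considerations gives feasible. The first lists several lights without combining them. The second acknowledges several outcomes but defines feasibility on one. The missing-data item pairs counts out of 100 with percentages of data, so it is unclear whether it counts participants or data points, and whether watch data enter.

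**8. Channels.** Food is logged in SH, and Study Procedures says that the GK app collects SH and watch data automatically. A food log could therefore be visible in GK data without any GK log-on, and the definition does not settle whether that week counts.

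**The case against.** The strongest reply is that the safeguard is already there. Missing data has its own light, and at the floor computed here it would be red. A reader might infer that the whole study can be declared green with about 93% of entries missing. The documents do not support that: only the acceptability light can be green in that situation, and the 8-week rule in Statistical Considerations corresponds to amber. What remains is that no rule says which light prevails, and that Statistical Considerations defines feasibility without the missing-data light.

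The 93% is also a floor and should not be read as a forecast. The plan includes daily ESAS prompts, app reminders and telephone calls, and nothing suggests that one entry a week is the expected pattern. That stands.

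A reader might also infer that entries made outside the GK app are miscounted. This is not shown. ESAS is completed in the GK app and one form a week suffices, so only someone who enters food or activity but no ESAS all week is affected. SH data reach the GK app. The watch also prompts ESAS, so its prompt for the weekly activity questions does not show that they are answered elsewhere. No frequency is given for the web survey. The treatment of such entries is undefined, which is a lesser fault.

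Nor do the documents show that the watch is ignored throughout. The specific hypothesis concerns the app, the focus group covers the watch, and a secondary-outcome subgroup uses app and watch completeness combined. Watch data may enter the missing-data light. The gap is established only for the engagement item.

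Finally, a low minimum-engagement threshold is a legitimate choice for a first pilot, and detailed counting rules may sit in a fuller document. That does not excuse two sections of this article giving different verdicts at the same level.

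**Conclusion.** The point holds in limited form. The acceptability light can be green with as little as 6.8% of a participant's scheduled entries supplied (5.4% to 10.7% over the denominators tried). At cohort level, green acceptability is compatible with up to 96.6% of these entries missing. These floors assume the Table 1 frequencies and one entry per qualifying week. That the missing-data light would then be red assumes that it is computed on these entries, which the article does not say.

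The main defect is the conflict between sections: Statistical Considerations calls feasible, on engagement alone, a level that Primary Outcome grades amber, and no rule resolves a disagreement between lights. The missing watch measure and the undefined status of SH food entries are secondary, but they bear on the main outcome and should be settled before analysis.

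**What to change.** 1. **Reconcile the two sections.** Feasible without modification should not follow from engagement alone or from the amber level. One option is to require also that neither the missing-data nor the attrition light is red. State the denominator of the missing-data percentage: participants or data points, which measures, and whether watch data are included. A strict rule that the worst colour decides is possible but debatable: on the 176 entries it would need about 106 per participant on average just to avoid red, against 8 for amber acceptability.
2. **Report completion beside engaged weeks.** Give ESAS days out of 112, food diaries out of 48, activity reports out of 16, and days with watch data out of 112. Watch data are already uploaded daily. Define what counts as a day with watch data, because sampling depends on user settings and charging. Limit any conclusion about the watch to that measure.
3. **Define the qualifying channels.** State either that time-stamped entries in any scheduled channel make a week engaged, or that only entries in the GK app do.

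The cost is protocol or SAP wording and a few tabulations, with no new data collection. The downside is that a favourable verdict becomes somewhat harder to reach.
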